## Abstract

**Background:**

Selective peripheral denervation via botulinum neurotoxin injections into dystonic muscles is the first-line treatment for cervical dystonia. Pallidal neurostimulation is a potent alternative, but currently restricted to patients failing on neurotoxin therapy. As botulinum neurotoxin is partially effective but often unsatisfactory in a relevant proportion of patients, earlier neurostimulation might be advantageous in providing stable symptom control and preventing disability. This trial intends to demonstrate, that pallidal neurostimulation is superior to neurotoxin injections in best clinical practice for controlling the symptoms of cervical dystonia and that it is safe in patients with a partial therapy response to peripheral denervation. We hypothesize a better outcome in everyday functioning and health-related quality of life of neurostimulated patients.

**Methods:**

We aim to recruit 66 cervical dystonia patients into a double-blind comparison of pallidal neurostimulation versus botulinum neurotoxin type A. Eligible patients need ≥25% motor symptom reduction 4 weeks after a neurotoxin test injection, but are willing to undergo DBS surgery due to unsatisfactory symptom control. All participants will be implanted with a DBS system, and randomized into 2 groups: First group will receive effective neurostimulation and saline injections into dystonic muscles. Second group is treated with regular neurotoxin injections and undergoes a sham-stimulation. Primary outcome is the change in TWSTRS total score between baseline and 6 months of therapy. Secondary outcome parameters are corresponding changes in TWSTRS motor score, Tsui score, CDQ-24 and SF-36. Safety will be assessed by frequency and severity of reported adverse events. Statistical analysis includes intention-to-treat and per protocol populations, analysis based on imputation of missing values and analysis adjusting for differences in baseline TWSTRS. After 6 months of blinded treatment all patients will receive open-label neurostimulation and neurotoxin treatment as needed, and are followed up 48 weeks after randomization.

**Perspective:**

We will assess if pallidal neurostimulation is a safe and effective alternative to selective peripheral denervation by botulinum toxin injections in cervical dystonia, which may be offered earlier in the course of disease based on patient preference. A positive study outcome would influence future treatment guidelines of cervical dystonia.

**Trial registration:**

EudraCT registration number:  2016–001378-13

## Background

Cervical dystonia (CD) is a central nervous system disease associated with involuntary muscle contractions, leading to repetitive or constant neck movements and partly bizarre head postures [1]. CD is estimated to be the most frequent of focal dystonias [9]. Activities of daily living, social participation and quality of life can be markedly impaired in CD due to pain, reduced active head and neck motion ranges as well as stigmatization (Camfield, Ben-Shlomo, Warner, & Epidemiological Study of Dystonia in Europe Collaborative, [4, 15]).

Chemical denervation via injection of botulinum neurotoxin (BoNT) into dystonic neck muscles is applied as first line treatment of CD; its efficacy and safety has been demonstrated in several randomized controlled trials [5, 18]. BoNT injections are shown to reduce mean symptom severity substantially defined as reduction between 9.7 to 11 points on Toronto Western Torticollis Rating Scale (TWSTRS) [2, 6]. In addition, its application is superior to pharmacological treatment with anticholinergic drugs [3]. As the neurotoxin effect is only temporary, repeated injections are necessary within a period of 8 to 16 weeks. Furthermore, the toxin effect builds up within a period of 1–4 weeks after injection; therefore, CD symptom severity tends to fluctuate during BoNT therapy. Beside these pharmacological response fluctuations, patients may experience a variable benefit from repeated injections, because the treatment is skill-dependent and limited by the reproducibility of applying equivalent toxin dosages into partly deep lying neck muscles. Beyond the principle efficacy established in pivotal trials, few studies have addressed the long-term efficacy and stability of BoNT treatment responses in daily practice. In an observational study Misra et al. reported that more than 60% of CD patients are treated satisfactorily with BoNT; however, considering the criterion of “duration of effect ≥ 12 weeks” reduced this proportion up to 29% [14]. A further limitation of BoNT therapy arises when complex dystonic patterns including tremor or jerky movements appear; in these cases, many muscles are involved in an intricate interplay, which apparently impedes a target-oriented injection. Additionally, dose-dependent adverse events (AE) may limit the treatment, such as neck weakness, dysphagia, dry mouth or dysphonia [7]. During chronic treatment, secondary therapy failure due to BoNT neutralizing antibodies develops in up to 5% of patients [10]. Despite these limitations and the discomfort associated with repeated BoNT injections, many patients adhere to this therapy, because they are not aware of potential alternatives.

Deep brain stimulation (DBS) is a surgical therapy for movement disorders, which retunes abnormal neuronal activity within motor circuits by continuous electrical stimulation of deep brain nuclei. DBS requires the surgical implantation of stimulating electrodes connected to a pacemaker device. There is class I evidence for the safety and efficacy of DBS applied to several brain targets (subthalamic nucleus, internal globus pallidus (GPi) and thalamus) for patients with Parkinson’s disease (PD) [8], tremor disorders [17] and dystonia [12]. Treatment effects of DBS are strong and can lead to almost complete symptom suppression even in severely disabled patients. Nevertheless, this therapy has been restricted to advanced disease stages after failure of pharmacological treatment alternatives out of principle safety considerations. DBS surgery carries a risk of permanent morbidity and mortality resulting from intracranial haemorrhage or infections, while the treated conditions are disabling but not life limiting by themselves. Otherwise, DBS may come too late in advanced disease stages for restoring function and societal participation in chronically disabled patients despite being effective on a symptom level. Improved surgical techniques and perioperative management have now reduced the chronic morbidity and mortality risk of DBS below 0.5% [11], which has allowed considering earlier DBS with the goal to maintain function and prevent psychosocial decline in PD. For example, the EARLYSTIM trial [16], a controlled randomized comparison of subthalamic DBS with best medical management of PD with early motor fluctuations has established superiority of DBS for improving off-period symptoms, response fluctuations and quality of life. Interestingly, there was no difference in the total number of AE and serious AE between both treatment groups over the 2 year study period, suggesting that the risks associated with medical treatment or inappropriate symptom control of PD have been largely underestimated in the past and may be mitigated by DBS.

GPi-DBS is an established first line therapy for patients with generalized dystonia, for whom no pharmacological treatment alternatives exist [12, 19]. Previous trials have also established efficacy and safety in patients with CD refractory to neurotoxin therapy. In a severely affected study population, a mean reduction of 5.2 points (26%) on TWSTRS motor and 18.3 points (40%) on TWSTRS total score was achieved by GPi-DBS [19]. Additionally, also pain, activities of daily living and quality of life are shown to improve during DBS treatment (Kupsch et al., 2006; [19, 20]).

Based on this evidence, we believe, that the acceptable safety profile and the therapeutic potency of DBS justify an earlier application in CD patients still responding to peripheral selective denervation, but suffering from incomplete symptom control or response fluctuations. In this trial we aim to prove that GPi-DBS leads to a superior symptom control in comparison to best clinical use of BoNT in the group of CD patients with a partial response to BoNT therapy. Consequently, we also hypothesize that dystonia-associated quality of life improves more with DBS treatment. Additionally, safety of DBS will be explored in this patient group.

## Methods/design

### Study protocol

Figure 1 shows the study schedule of StimTox-CD. During “screening visit” (SCR) a test BoNT injection is applied to prove partial therapy response of neurotoxin treatment. 4 (±1) weeks later in “evaluation visit” (EVA) treatment effect is quantified by clinical assessment comprising inter alia TWSTRS motor score. Finally, a minimal motor-symptom reduction of 25% is required to fulfil all inclusion criteria. Table 1 shows a comprehensive list of the criteria applied to choose eligible patients for the study.

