6 (±1) weeks after DBS implantation patients are divided in two study arms during “randomization visit” (RAN). Table 2 is showing the full data set, which is collected at RAN as baseline for the upcoming blinded study phase. Neurostimulation will be now activated for the first time and acute stimulation effects and adverse effects of all electrodes are tested in a structured fashion (“monopolar review”). In DBS group a local DBS expert implements an effective stimulation setting concerning stimulation amplitude and choice of electrodes after “best clinical practice” and a predetermined algorithm. Frequency must be adjusted to 130 Hz, pulse duration to 90 μs. In BoNT group stimulation amplitude is set to 0 V. This group is injected with BoNT by an experienced physician. The decision on preferred drugs (Onabotulinumtoxin A: BOTOX, Abobotulinumtoxin A: DYSPORT or Incobotulinumtoxin A: XEOMIN), applied dosage and injection technique (number of injections, injection site or guiding-techniques) is up to the discretion of the treating physician and supposed to correspond to best clinical practice. During the same visit, patients in DBS group get also injected, but only with saline. Neither patient nor treating physician is informed about the allocation to the study group, in the sense of a double-blind trial design. Obviously DBS setting is not appropriate to be implemented in a blind manner, what causes the need of two separate teams of physicians at each study site; one blinded (or BoNT) and one unblinded (or DBS) team.

**Table 2 Tab2:** Synopsis of interventions and data sets (displayed for single SimTox-CD study visits)

	Screening visit/SCR	Evaluation visit/EVA	DBS surgery/DBS	Randomization visit/RAN	Follow-up visit 1/FU1	Follow-up visit 2/FU2	Follow-up visit 3/FU3	Follow-up visit 4/FU4	Follow-up visit 5/FU5
timeline (weeks)	−14 (+/−1)	− 10 (+/− 1)	−6 (+/− 1)	0	+4 (+/− 1)	+ 12 (+/− 1)	+ 16 (+/− 1)	+ 24 (+/− 1)	+ 48 (+/− 1)
Interventions									
BoNT test injection	X								
DBS surgery			X						
Testing of stimulation (side) effects				X					
DBS setting/sham stimulation^a^				X		X			
Blind BoNT/placebo injection^a^				X		X			
Unblind neurostimulation								X	X
Randomization				X					
Data set									
Informed consent	X								
Inclusion/exclusion criteria	X	X							
Medical history	X								
Concurrent medication	X				X	X	X	X	X
TWSTRS	X	X		X	X	X	X	X	X
Tsui Rating Scale	X	X		X	X	X	X	X	X
Bain Tremor Rating	X	X		X	X	X	X	X	X
GCI	X	X		X	X	X	X	X	X

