### Statistics

Sample size calculation is based on primary outcome parameter TWSTRS total score change from baseline to FU4. The primary statistical analysis consists in a mean value comparison of the primary outcome between both treatment groups by the independent two-sample T-Test. For sample size calculation we refer to data from previously published studies. A GPi-DBS trial showed a mean therapy effect in TWSTRS total score in patients undergoing neurostimulation of minus 23.1 (±15.2 SD) points [19]. A mean maximum effect of neurotoxin treatment is described with minus 11.0 (±11.7 SD) points on TWSTRS total score at an average of 4 weeks after injection [6]. The resulting standardized mean difference of TWSTRS scores between both groups is 0.90. Using these assumptions a sample size of 2 × 28 = 56 patients ensures a power of 90% to detect this effect size as significant (at significance level 0.05) deviation from the null hypothesis (no difference between mean TWSTRS change scores in DBS and BoNT group). Taking into account a drop-out rate of 15% (conservative estimation) 2 × 33 = 66 must be randomized. Furthermore we assume that 20% of patients will refuse informed consent to undergo DBS after screening and another 20% will fail inclusion criteria of sufficient botulinum treatment response after test injection. Consequently, a total number of 2 × 52 = 104 patients will have to be screened to reach the calculated sample size.

Group comparisons for target variables with sample distributions compatible with the assumption of normality will be conducted by using the two-sided independent sample Student’s T-Test or the paired sample T-Test for within group comparisons (changes between visits). For variables with sample distributions not compatible with the assumption of normality non-parametric tests like Mann-Whitney-Test, Wilcoxon Signed Rank Test or Friedmann Test will be applied. Effects will be considered significant if *p* < 0.05.

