The primary statistical analysis of the primary outcome parameter as well as the secondary outcome parameter change in TWSTRS motor score, TSUI score and SF-36 score will be based on the intention-to-treat (ITT) population. To proof robustness of results two further analyses of sensitivity will be performed: the first one refers to all randomized patients with imputation of missing values after 6 months by appropriate methods of missing-data imputation depending on which missing-data mechanism could be reasonable. The second method includes only patients of per protocol (PP) population.

To address the question how much TWSTRS total score values differ between DBS and BoNT group on average, when patients would be start at baseline with the same score values, we will use ANCOVA (target variable: TWSTRS total change score from baseline to 6 months after operation, main factor: treatment method, covariate: baseline TWSTRS). Thereby we will adjust to imbalances in the TWSTRS distributions at baseline and the variance within the groups should be reduced.

Also for secondary outcome parameters an ANCOVA will be applied using treatment group as main factor, adjusted for each baseline variable as covariate. Furthermore longitudinal data of scores will be analysed by using GEE (generalized estimating equation) and linear models (“mixed models”). This will be helpful to describe interindividual variability of therapy response.

Safety analysis contains a structured list of AE of both study groups. Possibility of relation to study’s interventions will be judged by physicians of the unblinded team. Incidence of AE will be assessed by using Fisher’s Exact Test (analysis by patients: comparisons of proportions of patients with at least one corresponding event) and negative binomial regression (analysis by events: comparisons of counts of occurring events).

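### Three TWSTRS readings precede treatment, but the supplementary ANCOVA adjusts for one post-surgical reading, and no stated analysis uses the degree of toxin response beyond the 25% entry rule

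*Protocol article*

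**What the plan says.** The Study protocol section describes a toxin test injection at SCR and an assessment four weeks later at EVA, where "treatment effect is quantified by clinical assessment comprising inter alia TWSTRS motor score". Table 1 turns this into an entry criterion: at least a 25% fall in TWSTRS motor score, with no upper limit. No other use of that response is stated.

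Table 2 schedules TWSTRS and Tsui at SCR, EVA and RAN, and CDQ-24 and SF-36 at SCR and RAN. The protocol takes RAN as the baseline: "Table 2 is showing the full data set, which is collected at RAN as baseline for the upcoming blinded study phase". The Visit schedule section puts this six weeks after surgery, an interval chosen to lessen the surgical stun effect.

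In Statistics, the primary analysis is an unadjusted t-test on the change in TWSTRS total to FU4 (week 24). The ANCOVA is additional, and its terms are written out: "main factor: treatment method, covariate: baseline TWSTRS". The secondary outcomes get the same form, each with its own baseline. GEE and mixed models are also planned to describe variation in response between patients, without naming visits or covariates.

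**The concern.** Two things are left unused. The first is a second pre-treatment score. SCR is at least 12 weeks after the last toxin injection, RAN is 14 weeks after the test injection, and FU4 is 12 weeks after the FU2 injection. All three are readings late in an injection interval, and SCR is the one that surgery cannot have touched. It is a legitimate second covariate in a model that currently has one.

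The second is the test response. The Background argues that the evidence on DBS would "justify an earlier application in CD patients still responding to peripheral selective denervation", so degree of toxin response is the axis along which the trial extends DBS. The mean difference pools every response from 25% upward. A reader of a positive result will naturally ask whether the advantage of DBS shrinks as toxin works better, and no stated analysis addresses that.

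What is at stake is a modestly wider interval than necessary in a supplementary analysis, and an exploratory question that is more credible if specified before unblinding than after.

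**Working it through.** **Inputs from Statistics.** Assumed DBS change is "minus 23.1 (±15.2 SD) points", assumed BoNT change is −11.0 (SD 11.7), and the test is two-sided "at significance level 0.05". The plan states that "a sample size of 2 × 28 = 56 patients ensures a power of 90" per cent. The protocol gives no correlations between visits; all values below are assumptions.

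**The plan's own figure.** Pooled SD = √((15.2² + 11.7²)/2) = 13.56. Standardised difference = 12.1/13.56 = 0.892 (stated 0.90). The noncentral t distribution gives 90.6% power at 28 per arm. The stated sample size reproduces and is not in dispute.

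**What the planned ANCOVA already gains.** With equal correlation r between visits, and variance expressed relative to that of one visit:
- change score: 2(1 − r)
- ANCOVA with one baseline: 1 − r²
- ANCOVA with two baselines: 1 − 2r²/(1 + r)

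At r = 0.5 these are 1.00, 0.75 and 0.667. Scaled to a change-score SD of 13.56, power at 28 per arm is 90.6%, 96.6% and 98.0%. Most of the gain over the t-test is already in the one-baseline ANCOVA.

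**What SCR adds.** Let p be the partial correlation of SCR with FU4 given RAN. The variance of the adjusted difference changes by the factor (1 − p²) × 52/51, where 52/51 is the cost of one more covariate with 56 patients. Here p = (a − bc)/√((1 − b²)(1 − c²)), with a = SCR–FU4, b = RAN–FU4 and c = SCR–RAN.

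| a, b, c | 1 − p² | × 52/51 | Change in variance |
|---|---|---|---|
| 0.5, 0.5, 0.5 | 0.889 | 0.906 | −9% |
| 0.6, 0.6, 0.6 | 0.859 | 0.876 | −12% |
| 0.7, 0.7, 0.7 | 0.830 | 0.847 | −15% |
| 0.5, 0.6, 0.6 | 0.952 | 0.971 | −3% |
| 0.5, 0.6, 0.7 | 0.980 | 1.000 | 0% |
| 0.36, 0.6, 0.6 (full decay, p = 0) | 1.000 | 1.020 | +2% |

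Simulation of the three equal-correlation cases gave 0.909, 0.870 and 0.846, in agreement. A 15% fall in variance is about 8% on the standard error (√0.847 = 0.920). SCR is 38 weeks before FU4 and RAN is 24, so some decay is plausible and the lower rows deserve weight.

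**The interaction.** For a continuous test response in SD units, with correlation r to outcome in the toxin arm and none in the DBS arm, the SE of the slope difference is √(15.2²/28 + 11.7²(1 − r²)/28). This is 3.56, 3.45 and 3.28 points per SD for r = 0.3, 0.5 and 0.7. The slopes themselves would be r × 11.7 = 3.5, 5.9 and 8.2 points per SD, so normal-approximation power is about 16%, 40% and 70%. A median split does worse: SE = 13.56 × √(4/14) = 7.25 points, with 37% power even for an interaction as large as the whole 12.1-point effect.

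**Why the interval must not decide the conclusion.** Suppose the benefit is a uniform 12.1 points, with no effect modification. In simulation at 28 per arm, the interval from the interaction model favours DBS in about 61% of trials at 1 SD above the mean test response, and in about 30% at 2 SD. Imprecision alone would often exclude patients who benefit.

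**The case against.** The strongest reply is that extra covariates and exploratory interactions are usual content of an analysis plan, which is not shown, so their absence is silence rather than error. That stands for the interaction, which is why it is only an option here. It is weaker for the covariate, because the protocol does not leave the ANCOVA open: it names its terms.

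A reader might infer that the pre-surgery TWSTRS serves no purpose beyond entry. The documents do not support that. Randomization stratifies on baseline TWSTRS total without naming the visit, Table 1 uses baseline for the screening reading, and the longitudinal models name no visits. The SCR score may already be used in either place. Only for the toxin response is the 25% rule the sole stated use.

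A reader might also infer that the plan loses precision, or that the trial cannot show whether strong toxin responders benefit less. Neither follows. The one-baseline ANCOVA is more precise than the primary t-test over the correlations considered, RAN was a reasoned choice of baseline, and the response data are collected.

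Nor do the documents support a claim that the DBS advantage is small in strong responders. Any such figure rests on assumed correlations and on an SD of 11.7 that Statistics gives for about four weeks after injection, whereas FU4 is 12 weeks after. It would also relate a motor-score response to a total-score outcome and assume no association in the DBS arm. The test response comes from a single open injection and carries regression to the mean. Finally, the protocol already confines its claim to patients with partial, unsatisfactory toxin control.

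**Conclusion.** The point holds as an optional improvement with a small effect. As stated, the supplementary ANCOVA uses one of the available pre-treatment TWSTRS readings, and no described analysis uses the degree of toxin response after entry. The forgone precision is about 9 to 15% of variance under equal visit correlations of 0.5 to 0.7 and about 3% or less if SCR relates less to FU4 than RAN does. If SCR carries no information beyond RAN, adding it costs about 2%. The primary t-test and the sample size are unaffected. The value of the interaction is interpretive: it would give a pre-specified estimate on a question the trial's rationale raises, but too imprecise at 28 per arm to support a firm statement either way.

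**What to change.** 1. In the ANCOVA for TWSTRS total, add the SCR score as a second covariate beside the RAN score. Do the same with the SCR values of TWSTRS motor, Tsui, CDQ-24 and SF-36 in their ANCOVAs.
2. Optionally, pre-specify one exploratory model adding the continuous test response (per cent reduction in TWSTRS motor score from SCR to EVA) and its interaction with treatment. Report the interaction with its 95% CI, and state that it is imprecise at 28 per arm and that the response comes from one open injection.
3. Do not restrict the trial's conclusion by where that interval excludes zero.

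The cost is a few words in the analysis plan and one degree of freedom per ANCOVA, plus two more in the optional model. No new data, visits or patients are needed. If the unseen analysis plan already contains these terms, nothing needs to change.
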